#### Self-directed care pathway

The procedure for self-directed care pathway is similar to ICCC, except the participants will not have access to an AHLO to: (a) coordinate GP appointments at 1 week, 3 and 6 months post Paediatrician appointment, and (b) assist with any communication and access issues that arise during the duration of the study.

#### Outcome measures

Primary outcome measures taken at 1 week, 3, 6, 12 months include**:** PedQOL child module (Score 0 to 100; parent or child completed), [20] PedQOL family impact module (Score 0 to 100; parent completed), [20] SUDS (Score 0 to 100; parent completed), CBCL (Percentiles, parent completed) [21] and Rotter’s Locus of Control Scale (Score 0 to 23, parent completed) [22].

Secondary outcome measures taken at 1 week, 3, 6, 12 months include the number of**:** GP visits, hospital admissions**,** specialist appointments**,** absent school days, caregiver missed employment days, school suspensions including duration in days and services currently accessed at the time.

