#### Integrated Children’s care clinic (ICCC) pathway

At one week post Paediatrician appointment, the AHLO will make contact with the child’s General Practitioner (GP) to arrange a multidisciplinary long face-to-face meeting to help facilitate recommendations by the Paediatrician. This may include access to community allied health services. The child and caregiver will be seen by the GP at the conclusion of the multidisciplinary meeting for a consult. The AHLO will complete the following with the caregiver/child post GP consult (based on 7 day period):○ Ask how many services the child is currently accessing○ Number of days caregiver missed employment○ Collect baseline demographics data (family structure, primary carer education, primary carer employment status and mental health status). Please note: if caregiver reports emotional distress, then AHLO will recommend for caregiver to see their GP for further assistance.○ Complete Pediatric Evaluation of Disability Inventory (PEDI) if child is between 6 months to 7 years.

The AHLO will contact Education Queensland to request for number of school attendance and absent days, including any formal suspensions (if applicable). The AHLO will go through the following checklist to ensure completion. Liaison with other professionals and agencies will occur, as appropriate. Each process used and outcome will be documented to guide process evaluation for the AHLO role [19]. Please refer to Fig. 2, which outlines the logic model used to guide evaluation of the role of the AHLO in this trial. The AHLO will also submit Medicare forms to obtain information on the: number of GP visits, hospital admissions and specialist appointments for the preceding 7 days. Medical Students from each hospital will call the primary caregiver to complete the Pediatric Quality of Life (Ped QOL) Child and Family Impact Modules, [20] Subjective Units of Distress Scale (SUDS) and Locus of Control Questionnaire, and the opportunity to describe any other issues or concerns that they may have regarding their child.

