**Fig. 2 Fig2:**
[figure not shown]
Logic model outlining complex interactions of processes for proposed randomised control trial in the evaluation of an Allied Health Liaison Officer (AHLO). Abbreviations: AHLO – Allied Health Liaison Officer, GP – General Practitioners, Ped QOL – Pediatric Quality of Life, SUDS – Subjective Units of Distress Scale

At 3 months (+/− 14 days) post Paediatrician appointment, the AHLO will contact Education Queensland to request for number of school attendance and absent days, including any formal suspensions (if applicable). The AHLO will submit Medicare forms to obtain information on the number of GP visits, hospital admissions and specialist appointments for the preceeding timeframe between 1 week and 3 months post Paediatrician appointment. The AHLO will also help arrange a GP long face-to-face consultation appointment to review the child to check on progress of management plan in relation to the child’s chronic health condition. Finally, the AHLO will complete the following with the caregiver/child post GP consult: ask how many services the child is currently accessing, ask the caregiver how many days they had missed employment and complete the Child Behaviour Checklist (CBCL), [21] and further information that the caregiver would like to add about what issues the child and/or family might be encountering related to access to services/support.

At 6 months (+/− 14 days) post Paediatrician appointment, the AHLO will contact Education Queensland to request for the number of school attendance and absent days, including any formal suspensions (if applicable). The AHLO will also submit Medicare forms to obtain information on the number of GP visits, hospital admissions and specialist appointments for the preceeding timeframe between 3 months to 6 months post Paediatrician appointment. Finally, the AHLO will help arrange a GP long face-to-face consultation appointment to review the child. The AHLO will also call the caregiver to: ask how many services the child is currently accessing, ask how many days the caregiver missed employment and complete the CBCL [21]. Medical Students from each hospital will also call the primary caregiver to complete: Peds QOL Child and Family Impact Modules, [20] SUDS and Locus of Control Questionnaire.

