At 12 months (+/− 14 days) post Paediatrician appointment, medical students from each hospital will call the primary caregiver to complete: Peds QOL Child and Family Impact Modules, [20] SUDS and Locus of Control Questionnaire.

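### The outcome list gives four time points for every measure, but the visit procedures omit CBCL at 1 week and 12 months, four primary measures at 3 months, and all resource-use data after 6 months

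*Protocol article*

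**What the plan says.** The Outcome measures section of the protocol article sets one schedule for everything. "Primary outcome measures taken at 1 week, 3, 6, 12 months include" introduces five measures: PedQOL child, PedQOL family impact, SUDS, CBCL and Locus of Control. "Secondary outcome measures taken at 1 week, 3, 6, 12 months include the number of" introduces seven: GP visits, hospital admissions, specialist appointments, absent school days, missed caregiver work days, suspensions and services in use.

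The section on the ICCC pathway sets out each contact in detail, including who asks what.

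- **1 week.** The AHLO records services, missed work and demographics, and is told to "Complete Pediatric Evaluation of Disability Inventory (PEDI) if child is between 6 months to 7 years". School and Medicare data are requested. A separate call covers the rest: "Medical Students from each hospital will call the primary caregiver to complete the Pediatric Quality of Life (Ped QOL) Child and Family Impact Modules", with SUDS and Locus of Control. CBCL is not named.
- **3 months.** School and Medicare data are requested. The AHLO is to ask about services and "ask the caregiver how many days they had missed employment and complete the Child Behaviour Checklist (CBCL"). PedQOL, SUDS and Locus of Control are not named.
- **6 months.** School data are requested, and Medicare data cover "specialist appointments for the preceeding timeframe between 3 months to 6 months post Paediatrician appointment". The AHLO is to ask about services and "ask how many days the caregiver missed employment and complete the CBCL". Medical students take PedQOL, SUDS and Locus of Control.
- **12 months.** The whole entry is one call: "medical students from each hospital will call the primary caregiver to complete: Peds QOL Child and Family Impact Modules", plus SUDS and Locus of Control.

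The Self-directed care pathway section adopts a similar procedure. Its exceptions concern AHLO support, and it adds no assessment.

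**The concern.** Sites cannot follow both sections. The procedures are the operational text, so they are likely to govern what is collected.

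Two aims are exposed. Hypothesis (a) under Aims concerns quality of life and behavioural scores, and CBCL is the behavioural primary outcome. Under the procedures it has no value at the first assessment and none at 12 months. With about 50% attrition expected, a first value would help precision and help show whether drop-out was selective. It cannot be recovered later.

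Objective 2 and hypothesis (b) concern cost-effectiveness. Quality of life is followed to 12 months, but the last resource-use window closes at 6 months, so costs for months 6 to 12 would be absent.

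**Working it through.** The check compares the stated schedule with the visit procedures, cell by cell. PEDI is left out because it is not on the outcome list.

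**Stated (Outcome measures).** Primary 5 × 4 = 20; secondary 7 × 4 = 28; total 20 + 28 = 48.

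**Listed (ICCC pathway procedures, which the self-directed arm follows).**

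| Measure | 1 week | 3 months | 6 months | 12 months | Cells listed |
|---|---|---|---|---|---|
| PedQOL child | yes | no | yes | yes | 3 |
| PedQOL family impact | yes | no | yes | yes | 3 |
| SUDS | yes | no | yes | yes | 3 |
| Locus of Control | yes | no | yes | yes | 3 |
| CBCL | no | yes | yes | no | 2 |
| Each of the 7 secondary counts | yes | yes | yes | no | 3 each |

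- Primary: 4 × 3 + 2 = 14 of 20, so 6 are missing (30%).
- Secondary: 7 × 3 = 21 of 28, so 7 are missing (25%).
- Total: 14 + 21 = 35 of 48, so 13 are missing (13/48 = 27%).

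Cross-check by visit: 1 week 4 + 7 = 11; 3 months 1 + 7 = 8; 6 months 5 + 7 = 12; 12 months 4 + 0 = 4. The sum is 11 + 8 + 12 + 4 = 35. Only the 6-month visit is complete.

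**Which gaps matter.** Four of the 13 are the 3-month PedQOL (two modules), SUDS and Locus of Control entries. Rewording could settle these. The other 13 − 4 = 9 (CBCL twice, resource use seven times) carry the consequences described above.

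**Resource-use window.** Collection runs to 6 months and quality of life to 12, so 6 of the 12 months have no cost data.

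**The case against.** The strongest reply is that this is a condensed article. Data collection refers to Fig. 1 for the trial outline. The figure is not shown, and its caption names CBCL and the other scales, so it may carry the intended schedule. That is fair, and it limits the claim to what the procedures list, not what sites actually do. It does not remove the conflict, because a figure can agree with only one of two texts that disagree.

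It can also be said that the opening of the outcome list merely names measures used somewhere across four contacts. For the primary measures that reading is possible. For the secondary measures it is harder, since none is listed at 12 months.

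A reader might infer three stronger things, which the document does not support.

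- **That the CBCL comparison fails without a baseline.** Randomisation supports an unadjusted comparison at 6 months. Statistical analyses plans a Mann-Whitney test of quality of life with no baseline adjustment, and the sample size also rests on quality of life. A 1-week CBCL would not be a clean baseline in any case: the envelope is opened straight after consent, and in ICCC the 1-week AHLO items follow the GP consult.
- **That cost-effectiveness cannot be assessed.** Nothing names 12 months as the economic endpoint, and at 6 months all 12 measures are listed, so costs and quality of life can be matched there. The safety section also lets self-directed children change pathway after 6 months and drops their 12-month data, so 12-month comparisons are already limited.
- **That 12-month secondary outcomes are beyond recovery.** Five of the seven come from Medicare or Education Queensland records, which could be requested retrospectively. Only missed work and services in use depend on asking the caregiver.

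**Conclusion.** The inconsistency stands: 13 of 48 stated measure-by-time cells (6 of 20 primary, 7 of 28 secondary) do not appear in the visit procedures. If those are followed as written, CBCL has no first-assessment or 12-month value, the 12-month secondary outcomes are not collected, and costs can be matched to quality of life only up to 6 months. The 6-month randomised comparison is untouched.

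This assumes that the outcome list means each measure at each time, that the written procedures govern collection, and that the self-directed arm follows the same assessments. Fig. 1 could show which schedule was intended, but both sections would still need to agree.

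**What to change.** Reconcile the Outcome measures section with the visit procedures.

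1. **CBCL.** Add it to the first assessment, preferably completed before the envelope is opened, and reword Outcome measures to match, since neither section now has a pre-randomisation time point. Add it to the existing 12-month medical-student call.
2. **Resource use.** Either add the service-use and missed-work questions to the 12-month call and make one Medicare and Education Queensland request for months 6 to 12, or state that resource-use outcomes and the cost-effectiveness comparison run to 6 months only.
3. **3-month entries.** Either drop PedQOL, SUDS and Locus of Control at 3 months from the outcome list or add them to the 3-month procedures.
4. **12-month comparisons.** State that they are limited by the switching rule in the safety section.

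A secondary point: the AHLO delivers the intervention and also takes the CBCL. The medical-student callers could take it at both 3 and 6 months, which keeps the assessor the same across visits. Caregivers complete it and remain unblinded, so this removes only part of the possible bias.

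The cost is a protocol amendment, a longer first contact and 12-month call and, if resource use is extended, one extra records request per child. Moving the 3-month CBCL, or adding scales at 3 months, would also need a 3-month medical-student call, which the procedures do not now include. Recruitment began in October 2017, so children enrolled before the change will lack a first CBCL.

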## Methods

### Aims

This randomised controlled trial protocol investigates the cost-effectiveness of an integrated care pathway between hospital and primary care partnerships in improving health and social outcomes in children with chronic health conditions. More specifically, our objectives are to: (1) determine if the ICCC results in better health outcomes for children with chronic health conditions, compared to a self-directed care pathway; and (2) determine the cost-effectiveness of the ICCC using health economics data. We hypothesize that: (a) Children who access the ICCC will have improved quality of life and behavioural scores than children who access the self-directed care pathway; and (b) the ICCC pathway is more cost-effective than the self-directed care pathway.

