### Participants

Children aged 0 to16 years with a newly diagnosed chronic heath condition. Inclusion criteria:

Children aged 0 to 16 years who are seen by Paediatrician at Caboolture Hospital or GCUH and newly diagnosed with a chronic health condition where community based health or family support services are part of the management plan. Chronic health conditions are expected to last more than 6 months and to produce consequences that impact on the child’s quality of life [16]. Examples of chronic health conditions include (but are not limited to): Autism Spectrum Disorder (ASD), Attention Deficit Hyperactivity Disorder (ADHD), Intellectual Impairment (II), Specific Language Impairment (SLI), Oppositional Defiance Disorder (ODD), Fetal Alcohol Spectrum Disorder (FASD), Cerebral Palsy (CP).

Exclusion criteria: Children with acute medical conditions requiring urgent intervention where community follow-up is deemed inappropriate by the treating Paediatrician and /or children with a chronic medical condition primarily managed by medical consultation alone and those conditions where hospital based multidisciplinary teams provide coordinated care. Examples of excluded chronic health conditions include: cancer, cystic fibrosis, asthma and epilepsy.

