### Sample size and statistical power

We plan for a total sample size of 112 children (80% power to detect a mean effect difference of 15 between groups on the quality of life scale) at 0.05 significance level. This sample size has been adjusted for an anticipated high attrition rate of 50%. A 2-sample test of proportions will be used to compare baseline characteristics of both groups.

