### Statistical analyses

All analyses will be conducted using an “intention to treat” (ITT) analysis where all subjects will be compared in the groups which they were originally assigned (regardless of withdrawal or lost to follow-up). For our primary objective, Mann Whitney U test will be used to determine if differences in quality of life measures exist between the ICCC versus self-directed care groups.

For our secondary objective, we will perform univariable analysis to determine which health economic parameters (e.g. missed school days, number of hospital admissions) are related to higher quality of life scores. Stepwise regression will then examine the various combinations via of health economic parameters to generate area under receiver operating curves (aROC) to determine a clinical prediction index for higher quality of life scores. Parameters chosen will be based on using factors that were significant plus those with *P* < .25 level in the univariable analysis and other variables known to have a strong association with poorer health outcomes (e.g. multiple co-morbidities) within the literature. An aROC of ≥0.75 will be considered a clinically relevant cut-off score [23].

As this study is registered on the ANZCTR and occurring within Metro North Hospital and Health Service, the trial may be randomly audited by an independent study monitor at any timepoint in the study. A data monitoring committee will not be set up for the purposes of this study, as it is unblinded and not comparing rates of mortality or major morbidity.

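### CBCL, a primary outcome, is set on a percentile scale, a poor scale for differences or change; the power cost depends on the analysis, which the protocol does not name for CBCL

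*Protocol article*

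**What the plan says.** Under Outcome measures, the protocol article opens its list with "Primary outcome measures taken at 1 week, 3, 6, 12 months include" and includes "CBCL (Percentiles, parent completed"). The other four primary measures in that list are given as scores on a numeric range (0 to 100, or 0 to 23). CBCL alone is given as a percentile. No CBCL scale or subscale is named, and no rounding rule or upper limit is given.

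Under Aims, hypothesis (a) begins "Children who access the ICCC will have improved quality of life and behavioural scores", so behaviour is half of that hypothesis. CBCL is the only behaviour checklist among the primary outcomes.

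Under Statistical analyses, one between-group test is named: "Mann Whitney U test will be used to determine if differences in quality of life measures exist between the ICCC versus self-directed care groups". No test is named for CBCL.

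Under Sample size and statistical power, the trial is sized on quality of life only: "80% power to detect a mean effect difference of 15 between groups on the quality of life scale", "at 0.05 significance level", with a "total sample size of 112 children" after allowing for 50% attrition.

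Under Participants, children are "newly diagnosed with a chronic health condition where community based health or family support services are part of the management plan". The examples include ADHD, ODD and ASD, and also specific language impairment and cerebral palsy.

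**The concern.** A percentile is a bounded, non-linear transform of the score beneath it. Near the middle of the norm, a modest change in behaviour moves the percentile a long way. Near the top, a large change moves it by a point or two, and if percentiles are reported as whole numbers with a ceiling, many children tie there.

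Two things are at stake. The first is interpretation: the same true improvement gives a different difference in percentile points depending on where the children start, so an effect estimate on this scale cannot be read without the baseline level. The second is power: an analysis of means or of change on percentiles gives little weight to improvement in the most affected children. With these diagnoses, raised scores are plausible for many participants, although the document gives no figure for them.

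**Working it through.** **Inputs from the protocol.** Total 112; attrition 50%; equal allocation; alpha 0.05 (taken as two-sided, since this is not stated); 80% power for a 15-point difference in quality of life.

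**The plan's own figure.** The SD is not stated, so 112 cannot be reproduced from the text alone. With an assumed SD of 20:

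- n per arm = 2 × (1.960 + 0.842)² × (20/15)² = 27.9, rounded up to 28
- evaluable total = 2 × 28 = 56
- total = 56 / (1 − 0.50) = 112

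This agrees with the plan. It implies a standardised effect of 15/20 = 0.75 SD. I borrow 28 per arm and 0.75 SD for CBCL purely as a yardstick; the protocol gives no CBCL effect.

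**Compression.** Assume a normal norm with mean 50 and SD 10, and percentile = 100 × Φ((T − 50)/10). Then T 50, 60, 70 and 80 lie at percentiles 50.0, 84.1, 97.7 and 99.9. An improvement of 10 T points (1 SD) therefore moves:

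- from T 60 to T 50: 84.1 − 50.0 = 34.1 percentile points
- from T 80 to T 70: 99.9 − 97.7 = 2.2 percentile points (2.1 before rounding)

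**Meaning of a mean difference.** If the underlying score is normal with mean μ and SD 1 in norm units, the mean percentile is 100 × Φ(μ/√2). The same 0.75 SD improvement then gives:

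- μ = 1: 100 × [Φ(0.707) − Φ(0.177)] = 76.0 − 57.0 = 19.0 points
- μ = 1.5: 100 × [Φ(1.061) − Φ(0.530)] = 85.6 − 70.2 = 15.4 points
- μ = 2: 100 × [Φ(1.414) − Φ(0.884)] = 92.1 − 81.2 = 10.9 points (11.0 before rounding)

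**Power.** Simulation with 20,000 replicates, 28 per arm, control N(μ, 1), ICCC N(μ − 0.75, 1), and percentiles rounded to whole numbers and capped at 1 and 99. The Monte Carlo standard error is about √(0.76 × 0.24 / 20,000) = 0.3 points.

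| Control mean above norm | Controls at the cap | t-test: underlying score → percentile | Mann-Whitney: underlying score → percentile |
|---|---|---|---|
| 1 SD | 12% | 78.1% → 74.8% (loss 3.3) | 75.5% → 75.6% (none) |
| 1.5 SD | 25% | 78.4% → 71.7% (loss 6.7) | 76.2% → 75.8% (loss 0.4) |
| 2 SD | 43% | 78.7% → 64.6% (loss 14.1) | 76.0% → 73.8% (loss 2.2) |

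With percentiles neither rounded nor capped, Mann-Whitney power is identical on both scales, as it must be, because a percentile preserves rank order.

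**Sensitivity.** A separate simulation with whole-number T-scores and uncapped percentiles gave t-test losses of about 3, 7 to 8 and 13 points at 1, 1.5 and 2 SD. With an assumed lower cap at the 98th percentile, Mann-Whitney lost about 1 point at 1.5 SD and 4 at 2 SD. It lost 11 to 13 at 2.5 SD, where over 70% of controls sit at the cap.

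These figures concern a comparison at a single visit. An analysis of within-child change was not simulated. It has the same defect, because a difference of percentiles is not a monotone transform of the difference in scores, so ranking the changes does not restore the invariance.

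**The case against.** The strongest reply is that the only between-group test in the protocol is rank-based. Under Mann-Whitney, compression alone costs nothing; only ties do, and how many ties there are rests on a cap, a spread and a mean that the document does not give. The population is mixed, and clustering at a ceiling is plausible but not shown. Sample size and the named test both concern quality of life, not CBCL. The word in brackets may only describe how the instrument is reported, with the analysed score left to a fuller plan. Percentiles also have a real merit: they are norm-referenced, which helps when ages run from 0 to 16.

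Most of this stands. A reader might infer from the percentile scale that the trial, as written, wastes power on CBCL. The document does not support that: it plans no comparison of CBCL means, and under the kind of test it does name the loss is negligible unless many children tie at a ceiling.

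Three things remain. The scale is a stated choice for a primary outcome, not a missing detail. The Mann-Whitney sentence is worded for quality of life, so nothing ensures that CBCL will be analysed by ranks. And rank invariance protects a p-value at one visit; it does not give meaning to an effect in percentile points, nor does it protect an analysis of change. The merit of norm-referencing is kept in full by a standardised score.

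**Conclusion.** The point holds as one about scale, and it is minor. Percentile points are a poor unit for CBCL differences or change, because the same improvement reads as about 19 points at 1 SD above the norm and 11 at 2 SD.

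The power cost is conditional. With a Mann-Whitney test it is about nil at 1 to 1.5 SD and 2 to 3 points at 2 SD with a cap at 99. With a comparison of means it is about 3, 7 and 14 points at 1, 1.5 and 2 SD; for an analysis of change these serve only as a guide. The CBCL mean, spread, effect of 0.75 SD, rounding and cap, and the 28 children per arm at analysis, are all assumptions. A general claim of lost power should not be drawn from this, nor any change to the total of 112, which was set for quality of life.

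**What to change.** Under Outcome measures, replace the percentile with the norm-referenced standardised CBCL score from which it is derived, name the CBCL scale to be used, and keep percentiles for description. Under Statistical analyses, say which test applies to CBCL. Raw scores are not a suitable substitute here, because they are not norm-referenced across ages 0 to 16.

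The cost is a change of wording: the same completed form supplies both scores, and neither data collection nor sample size changes.

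While editing, reconcile the CBCL visits. Outcome measures lists 1 week, 3, 6 and 12 months, whereas the visit descriptions under Data collection schedule CBCL at 3 and 6 months only. That is a separate matter, but it decides whether any change from the first visit can be analysed at all.
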